**Methods:**

This study is a randomized controlled trial (RCT). Fifty children with ASD and anxiety, aged 7 to 13 years, will be randomly assigned to group CBT or a wait-list control (WL) condition. The design will follow a two (CBT and WL) by two (pre–post assessment) mixed between–within design. The control group will receive intervention after the waitlist period of 13 weeks. Primary outcomes are diagnostic status and severity of the anxiety disorders, measured with The Anxiety Disorder Interview Schedule for DSM-IV, Parent and Child Versions. Secondary outcomes are parent and child ratings on questionnaires on the child’s level of anxiety and impact on everyday life. Additional outcomes entail information gathered from parents, child and teachers on the child’s behavior and negative self-statements, together with social and adaptive skills. Follow-up data will be collected 3 months after intervention.

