### Outcome measures (Table 2)

#### Primary outcome

The primary outcome measure will be diagnostic status of the primary anxiety disorder measured with ADIS-IV-C/P [35]. ADIS-IV-C/P is a structured interview conducted with both child and parents designed to assess for current episodes of anxiety disorders, and to permit differential diagnosis among the anxiety disorders according to DSM-IV criteria. Further to the assessment of anxiety disorders, the ADIS-IV-C/P allows for assessment of other disorders such as depression, dysthymia, oppositional disorder, conduct disorder, and ADHD. In this study, only the sections regarding anxiety disorders along with OCD, depression, and dysthymia will be assessed.

**Table 2 Tab2:** Overview of measurements

		CBT			WL			
Outcome	Scale	T1	T2	T3	T1	T1’	T2’	T3’
Sociodemographics	Developed by authors	✓			✓			
Child anxiety disorder	ADIS-IV-C/P	✓	✓	✓	✓	✓	✓	✓
Child co-morbid disorder (obsessive compulsive disorder and depression)	ADIS-IV-C/P	✓	✓	✓	✓	✓	✓	✓
Child anxiety symptoms	SCAS	✓	✓	✓	✓	✓	✓	✓
Life interference from anxiety	CALIS	✓	✓	✓	✓	✓	✓	✓
Attention deficit hyperactive disorder	ADHD-RS	✓	✓	✓	✓	✓	✓	✓
Social and communicative skills	SRS	✓	✓	✓	✓	✓	✓	✓
Behavioral and emotional problems	SDQ	✓	✓	✓	✓	✓	✓	✓
General measure of negative self-statements	CATS	✓	✓	✓	✓	✓	✓	✓
Child adaptive skills	ABAS-II	✓		✓		✓		✓
Parent quality of life	WHO-5 + PSE	✓	✓	✓	✓	✓	✓	✓
Program evaluation	ESQ		✓				✓	

*T1* baseline assessment, *T2 + T1’* 13 weeks after baseline, *T3* 25 weeks after baseline, *T2’* 13 weeks after T1’-baseline, *T3’* 25 weeks after T2’-baseline. Primary outcome: *ADIS-IV-C/P* Anxiety Disorders Interview Schedule for DSM-IV: Parent & Child interview schedule; Secondary outcomes: *SCAS* Spence Children’s Anxiety Scale, *CALIS* Children’s Anxiety Life Inference Scale; Other outcomes: *ADHD-RS* Attention Deficit/Hyperactive Disorder-Rating Scale, *SRS* Social Responsiveness Scale, *SDQ* Strengths and Difficulties Questionnaire, *CATS* Children’s Automatic Thoughts Scale, *ABAS-II* Adaptive Behavior Assessment System, Second Edition, *WHO-5* WHO-five Well-being Index + 10 questions regarding depression from Present State Examination, *ESQ* Experience of Service Questionnaire

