### Analysis

The primary outcome will be measured as a dichotomous variable, as one (1) if the primary anxiety disorder identified before treatment (at time point T1) persists post treatment (T2) and as zero (0) if the child no longer fulfils diagnostic criteria for the primary anxiety disorder at T2.

The overall percentage of children free of primary anxiety disorder will be calculated and the effect of the intervention will be measured in terms of odds ratio, comparing odds for recovery in the treatment condition with the corresponding odds in the control condition. This will be calculated by conditional logistic regression and with adjustment for sex and co-morbidity (yes/no) by diagnoses other than anxiety disorders and ASD.

A mixed between–within analysis of variance (ANOVA) design will be used for all continuous outcomes to further evaluate the effect of the CBT intervention. Possible reduction in scale scores on CSR, SCAS, CALIS, ADHD-RS, SDQ, SRS, CATS, and ABAS-II, together with measures of parent’s quality of life, will be investigated to test for differences between CBT and WL groups while comparing pre and post measures within the two groups.

Analysis of the treatment effect such as direct comparison between T1/T1’ and T3/T3’ or changes over time (from T1/T1’ via T2/T2’ to T3/T3’) in the different scale scores may also be considered regarding further elucidation of CBT efficacy.

In order to enhance the strength of the analysis regarding continuation at follow-up (T3 and T3’) of the treatment effect seen at T2 and T2’, the possibility of combining CBT and WL groups will be investigated. However, we are aware that baseline levels at T1’ can be different from T1 due to natural fluctuation, which means that the two samples may not compare well. Thus, combining the samples will only be done after investigating such possible differences at baseline levels.

Repeated measures (longitudinal) analyses will be used when relevant. It is unlikely that the same probability distribution can be used for all secondary outcomes and statistical inference will determine which to apply. For some measures, a normal distribution may be applied, whereas other measures are nominal or at best ordinal.

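### The Analysis section, the Study procedure section and Table 2 disagree on when ABAS-II is collected; if Table 2 governs, the planned CBT-versus-WL pre/post test of adaptive skills has no data to run on

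*Protocol article*

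**What the plan says.** Three places in the protocol article bear on ABAS-II.

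- **Analysis.** The method is stated generally: "A mixed between–within analysis of variance (ANOVA) design will be used for all continuous outcomes". The scales are then listed: "Possible reduction in scale scores on CSR, SCAS, CALIS, ADHD-RS, SDQ, SRS, CATS, and ABAS-II". The contrast is "to test for differences between CBT and WL groups while comparing pre and post measures within the two groups". The Abstract gives the same structure, a "two (CBT and WL) by two (pre–post assessment) mixed between–within design".
- **Outcome measures, Table 2.** The row for "Child adaptive skills" (ABAS-II) is ticked at T1 and T3 for CBT and at T1' and T3' for WL. It is blank at T2 for CBT and at T1 and T2' for WL. The legend places T2 (CBT) and T1' (WL) at the same time, 13 weeks after baseline, and T3 at 25 weeks. The Primary outcome section confirms that T1' in the WL arm is the T2 assessment.
- **Study procedure.** Questionnaires for secondary and other outcomes go out two to three weeks before CBT or the wait starts, and families complete them again after treatment or the wait and at follow-up. No exception is made for ABAS-II, which the Table 2 legend and the Other outcomes section place among the other outcomes.

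**The concern.** A pre/post comparison between randomised arms needs each arm measured at the start and the end of the randomised period. Table 2 gives ABAS-II at only one end in each arm: the start for CBT and the end for WL. The Analysis section nevertheless treats ABAS-II like the scales collected at every visit. Two explicit statements conflict here, so this is not a detail that an article leaves to a fuller plan. An analysis plan cannot supply values that were never scheduled.

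At stake is whether the trial can say anything randomised about adaptive skills. If the conflict is found only at analysis, the comparison must be dropped or replaced after the data are in. The replacement nearest to hand, change from before CBT to the three-month follow-up in both arms, has no untreated group.

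**Working it through.** No figure in the plan depends on this point. The one calculated figure, 17 per group for 60% against 10% with a two-sided Fisher's exact test, is reproduced: exact power is 78.6% at 16 per group and 82.7% at 17. It concerns the ADIS outcome only.

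**Step 1: what the planned test needs.** Write M(arm, visit) for the mean ABAS-II score. The group-by-time effect over the randomised 13 weeks is

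[M(CBT, T2) − M(CBT, T1)] − [M(WL, T1') − M(WL, T1)].

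**Step 2: what Table 2 supplies.**

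| Cell needed | Visit | ABAS-II in Table 2 |
|---|---|---|
| CBT, pre | T1 | ticked |
| CBT, post | T2 | blank |
| WL, pre | T1 | blank |
| WL, post | T1' | ticked |

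Two of the four terms are absent. The trial plans five blocks of ten, five children per arm in each, so 25 per arm and 50 in all. Under this schedule the number with both values over the randomised period is 0 of 25 for CBT plus 0 of 25 for WL, that is 0 of 50.

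**Step 3: whether the remaining data can stand in.**

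- *Post-only comparison.* This needs CBT T2 against WL T1'. CBT T2 is blank.
- *CBT T1 against WL T1'.* The arms are measured 13 weeks apart, so arm and time are confounded, and neither group has yet had CBT.
- *CBT T3 against WL T1'.* These lie 25 and 13 weeks after baseline, so arm and time are again confounded.
- *Change T1 to T3 (CBT) against T1' to T3' (WL).* Both intervals contain the CBT programme. Each estimates change around treatment, and neither is a control for the other.
- *Multiple imputation.* The plan offers it for drop-out. Here a whole arm is unmeasured at a visit by design, so no observed ABAS-II value informs the within-child change.

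**Step 4: whether the blanks could be a fault in reading the table.** The ABAS-II row has all nine cells (two labels and seven visits), as do the CALIS, sociodemographic and ESQ rows, which align sensibly. The ABAS-II ticks also form a coherent pattern in each arm: before treatment and at follow-up.

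**Step 5: whether other scales are affected.** SCAS, CALIS, ADHD-RS, SDQ, SRS, CATS and the parent quality-of-life measure are ticked at all four needed visits. CSR comes from the ADIS-IV-C/P row, which is also complete. Only ABAS-II is affected.

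**The case against.** The strongest reply is that Table 2 may be the place in error. The Study procedure section, read literally, has families completing all other-outcome questionnaires before and after CBT or the wait, and the Analysis section assumes the same. Two narrative sections therefore stand against one table row. The Table 2 legend also looks imperfect: it counts T3' from T2', whereas it counts T3 from T1. The SPIRIT figure that might settle the matter is not shown here. This part of the objection stands. A reader might infer from Table 2 that the comparison simply cannot be done and that no randomised ABAS-II data exist. The article does not support that without the condition that Table 2 governs. The condition is plausible, since the row looks deliberate, and the Study procedure sentence on repeat completion mentions families only, while the Discussion says ABAS-II also comes from teachers.

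A second reply is that the Analysis section has a use for the T1/T1' and T3/T3' values: it says a direct comparison between them may be considered, and it warns that T1' levels can differ from T1. That fits the ABAS-II schedule exactly. It is, however, optional and uncontrolled, and it does not remove ABAS-II from the between-group list.

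A reader might also infer that the available pairs will be put into the two-by-two ANOVA, giving an effect near zero that is then misread as no benefit. Nothing in the article says the pairs will be used so, and an expected effect near zero would further require equal response to CBT in both arms. That is a risk to guard against, not a consequence of the plan.

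**Conclusion.** The inconsistency is real: the three sections cannot all be right about ABAS-II. On the condition that Table 2 is the schedule in force, two of the four design cells are empty, no child contributes a pair over the randomised 13 weeks, and the CBT-versus-WL group-by-time effect is not estimable. If the Study procedure section is in force instead, the analysis is feasible for family-reported ABAS-II and the Table 2 row is wrong. The article does not settle which.

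The size is minor to moderate. ABAS-II is one of several scales in the third outcome tier. The ADIS-based primary outcome, SCAS, CALIS and the sample size of 50 do not depend on it, so the point should not be read as a threat to the trial's main conclusions.

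**What to change.** First establish which schedule the trial follows, and make the Study procedure section, Table 2 and the Analysis section agree.

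- **If ABAS-II is in fact collected before and after CBT or the wait in both arms,** correct the Table 2 row and state whether this covers teachers as well as parents. The cost is an edit.
- **If Table 2 is right and the between-group test is wanted,** add ABAS-II at CBT T2 and WL T1 for blocks not yet past those visits. Both visits already exist, so the cost is one more parent and teacher form per arm. Each block is randomised 1:1, so later blocks still give a randomised comparison, but with only five children per arm per block. The report should state how many blocks contribute. The Trial status section gives a start in August 2016 and an expected finish by mid-2018, so few or no blocks may remain.
- **If Table 2 is right and nothing is added,** remove ABAS-II from the list of scales in the between-group pre/post analysis. Report it as within-child change from T1/T1' to T3/T3', labelled as uncontrolled. The cost is one line of text and the loss of a between-group result for ABAS-II that this schedule could not have given.

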## Discussion

Findings from Australia provide the first evidence for the benefit of this manualized CBT program for children with ASD and co-morbid anxiety disorders [25]. In order to investigate whether the findings regarding the effect of the CBT program can be confirmed in a broader international population this RCT aims to determine the effectiveness of the Cool Kids ASD program in Danish children and, more importantly, aims to demonstrate effects within a real-world, mental health clinic setting.

A limitation of this study could be the choice of anxiety assessment tool since the ADIS-IV-C/P is designed for typically developing children and their manifestations of psychopathology, and might thus not be as reliable and valid in children with ASD [55]. However, no validated anxiety assessment tool for children with ASD is presently available, leaving the ADIS-IV-C/P as the most used assessment tool in this line of research.

Another possible limitation is that a sample of 50 allows for detection of a relatively large effect and, thus, if treatment effects differ by a smaller effect, the study is underpowered. Finally, the use of a WL control condition controls for the simple effects of time, but does not allow conclusions about the specificity of treatment components.

A key strength of this study is its delivery in a real-world clinical setting, using practicing clinical staff. To our knowledge, most similar studies have been placed at university clinics and this will be one of the first studies showing the effect of a manualized CBT program for anxiety in children with ASD in a public mental health clinic setting.

Another strength is the use of outcome measures containing information from a variety of reporters. ADIS-IV-C/P, SCAS, and CALIS are obtained from both parents and children, and ADHD-RS, SDQ, SRS, and ABAS-II from parents and teachers separately. Teachers are found often to be more accurate in evaluating children’s function and behavior, especially with regards to social difficulties, than parents [56].

The literature suggests that structured intervention like the manualized CBT group program will not only improve the main presenting difficulty, but also other aspects of the participant’s functioning such as peer relationships [57]. Training anxiety reduction skills and, thus, decreasing anxiety in children with ASD using the manualized CBT program has the potential of preventing relapse and ensuring better psychosocial development for the child in general. Therefore, the reduction of anxiety symptoms and maybe even of symptoms of other co-morbid disorders may have a great impact on the severity of ASD and, in addition, may aid in improving quality of life for the whole family.

Further perspectives of this study are the contribution to future research in this field and the possibility of translation of an effective treatment for anxiety in children with ASD into daily clinical practice.

### Trial status

A pilot study of five children and their parents was performed in the autumn of 2014, showing almost 50% reduction in the children’s anxiety symptoms (SCAS) [45] and 60% reduction in the interference of anxiety in the children’s lives (CALIS) [46]. In addition, the program received very good satisfaction scores from all the families. A further pilot study with 20 children allocated randomly to CBT or treatment as usual (consisting of five sessions of ASD-based instructions) was performed at the beginning of 2016 (results not yet available). Based on both the pilot studies and the experience from running the program at Macquarie University, Sydney, the treatment manual has been under revision resulting in a second version. This RCT study began in August 2016 and the final group is expected to be recruited and to finish the program by mid-2018.

## Abbreviations

ABAS-II: Adaptive Behavior Assessment System Second Edition
ADHD: attention deficit hyperactive disorder
ADHD-RS: Attention Deficit/Hyperactive Disorder-Rating Scale
ADIS-IV-C/P: Anxiety Disorders Interview Schedule for DSM-IV: Parent & Child interview schedule
ASD: autism spectrum disorder
CALIS: Children’s Anxiety Life Inference Scale
CATS: Children’s Automatic Thoughts Scale
CSR: clinical severity rating
CBT: cognitive behavioral therapy
OCD: obsessive compulsive disorders
SCAS: Spence Children’s Anxiety Scale
SDQ: Strengths and Difficulties Questionnaire
SRS: Social Responsiveness Scale
